**Inclusion criteria**	
- Age 18 to 70 years old	
- Mild to moderate SUI or MUI (with predominance of SUI) as assessed by means of the 1-h pad test (leakage ≥ 2 g). Mild SUI will be defined as leakage up to 10 g and moderate SUI as leakage of 11 to 50 g [17]	
- Able to have a gynaecological examination	
**Exclusion criteria**	
- Symptoms of overactive bladder alone	
- Chronic degenerative, uncontrolled metabolic, neurological or psychiatric diseases	
- Previous participation in a pelvic floor re-education programme and/or previous pelvic floor surgery or currently receiving other treatment for UI	
- Pelvic organ prolapse greater than stage II according to the Pelvic Organ Prolapse Quantification (POP-Q) system	
- Use of medication for UI or medication that interferes with the musculoskeletal system	
- Loss of stools or mucus	
- Active urinary or vaginal infection in the past 3 months	
- Body mass index ≥ 35 kg/m^2^	

### Interventions

The participants will perform PFM exercises for 14 weeks in individual outpatient sessions supervised by an experienced physical therapist with training in pelvic floor rehabilitation. On weeks 1 and 2, the PFM training programme will be presented and taught (two outpatient weekly sessions) as per the allocation group. From weeks 3 to 14, the participants will perform PFM strength training, power and hypertrophy. The exercise programme for the first month will begin with a single outpatient session; then, the participants will perform the exercises at home and will visit the outpatient clinic 15 days later to resolve possible doubts and train under the supervision of a physical therapist [26]. At the end of the first month of training, the participants will visit the outpatient clinic to enhance the training programme by aiming to achieve greater recruitment of the involved muscles and avoid muscle adaptation [25]. The training protocol will be divided into three stages to allow for gradual progression of treatment. This is to say, the exercises will be gradually enhanced in the terms of duration, number of repetitions and position. Each stage will last 4 weeks (Table 3).

**Table 3 Tab3:** Details of the monthly training programmes

	The Knack group	PFMT group	PFMT + the Knack group
**Weeks 1–2**	Presentation and explanation of the exercise programme	Presentation and explanation of the exercise programme	Presentation and explanation of the exercise programme
**Weeks 3–6 (1st month)**	3 exercises in supine position: 8 repetitions (1 series) of each exercise 3 times per day, 3 days per week for a total of 108 monthly series + orientation to perform the Knack during ADL and WA	8 MVC of PFM in supine position sustained for 6 s (type I muscle fibres) with a resting interval twice as long between contractions, followed by 3 fast contractions (type II muscle fibres) 3 times per day, 3 days per week, for a total of 36 monthly series	8 MVC of PFM in supine position sustained for 6 s (type I muscle fibres) with a resting interval twice as long between contractions, followed by 3 fast contractions (type II muscle fibres) 3 times per day, 3 days per week, for a total of 36 monthly series 3 exercises in supine position: 8 repetitions (1 series) of each exercise 3 times per day, 3 days per week for a total of 108 monthly series + orientation to perform the Knack during ADL and WA
**Weeks 7–10 (2nd month)**	3 exercises in sitting position: 8 repetitions (1 series) of each exercise 3 times per day, 3 days per week for a total of 108 monthly series + orientation to perform the Knack during ADL and WA	8 MVC of PFM in sitting position sustained for 8 s (type I muscle fibres) with a resting interval twice as long between contractions, followed by 4 fast contractions (type II muscle fibres) 3 times per day, 3 days per week, for a total of 36 monthly series	8 MVC of PFM in sitting position sustained for 8 s (type I muscle fibres) with a resting interval twice as long between contractions, followed by 4 fast contractions (type II muscle fibres) 3 times per day, 3 days per week, for a total of 36 monthly series 3 exercises in sitting position: 8 repetitions (1 series) of each exercise 3 times per day, 3 days per week for a total of 108 monthly series + orientation to perform the Knack during ADL and WA
**Weeks 11–14 (3rd month)**	4 exercises in standing position: 8 repetitions (1 series) of each exercise 3 times per day, 3 days per week for a total of 144 monthly series + orientation to perform the Knack during ADL and WA	8 MVC of PFM in standing position sustained for 10 s (type I muscle fibres) with a resting interval twice as long between contractions, followed by 5 fast contractions (type II muscle fibres) 3 times per day, 3 days per week, for a total of 36 monthly series	8 MVC of PFM in standing position sustained for 10 s (type I muscle fibres) with a resting interval twice as long between contractions, followed by 5 fast contractions (type II muscle fibres) 3 times per day, 3 days per week, for a total of 36 monthly series 4 exercises in standing position: 8 repetitions (1 series) of each exercise 3 times per day, 3 days per week for a total of 144 monthly series + orientation to perform the Knack during ADL and WA

*MVC* maximum voluntary contraction, *s* seconds, *ADL* activities of daily living, *WA* work-related activities

Although there are no known side effects or complications from PFMT—besides possible discomfort after intervention—the occurrence of any adverse events will be monitored. All the participants will be instructed to contact the investigators in case they exhibit some adverse events at any time throughout the study.

### Outpatient sessions

The participants will perform 45-min individual PFM exercising sessions. The exercises will be performed in the supine (first month), sitting (second month) and standing (third month) positions. During the sessions, the participants will be verbally commanded to perform a series of PFM exercises under the supervision and encouragement of a physical therapist (Table 3). By the end of this 3-month training period, the participants will have attended six outpatient sessions (two per month).

### Home PFM exercises

The participants in all groups will be encouraged to perform three daily series with eight repetitions 3 days a week throughout the 3-month training period. The exercises will be performed in the supine (first month), sitting (second month) and standing (third month) positions (Table 3).

#### Group I (the Knack)

The participants will perform the Knack (Additional file 2) at the outpatient clinic and at home. The Knack consists of voluntary PFM contractions before and during activities that increase abdominal pressure. Such contraction elevates the pelvic floor cranially, with consequent closure of the urethra, vagina and rectum [11], stabilisation of the pelvic floor [12, 16] and avoidance of urine leakage [16].

Participants who are unable to perform the indicated exercises because of some physical limitation will undergo a process of adjustment according to their physical conditions. In addition to the protocol, the participants will be instructed to perform PFM contraction before and during any effort associated with daily living (ADL) and work-related (WA) activities (coughing, sneezing, laughing, walking up and down stairs, jumping, running, bending) [16].

#### Group II (PFMT)

These participants will perform PFMT at the outpatient clinic and at home. This protocol is based on studies by Bø et al. [27] (Additional file 3). The rationale underlying intensive PFM strength training is that it might develop the structural support of the pelvis by raising the levator plate to a permanent, higher position within the pelvis and promoting PFM and connective tissue hypertrophy and stiffness. These conditions facilitate automatic and more efficacious activation of motor units (neural adaptation), which impedes descent during activities that increase abdominal pressure [11].

#### Group III (the Knack + PFMT)

These participants will perform the exercises described for both the Knack and PFMT groups at the outpatient clinic and at home (Additional file 2 and 3).

### Criteria for discontinuing or modifying allocated intervention

There are no special criteria for discontinuing or modifying allocated interventions. Participants can choose to stop the treatment proposed in the study at any time before the results are published.

### Strategies to improve adherence to interventions

To motivate and improve adherence to at-home training, the participants will receive adhesive labels (of discrete colour) to place at strategic locations (computer, television set, furniture) at home or the workplace to remind them to perform the indicated exercises [28].

### Relevant concomitant care permitted or prohibited during the trial

During the protocol, medical consultations and the intake of medications are allowed, with the exception of medication or another treatment for urinary incontinence.

### Standardisation of treatment

The physical therapist who will be delivering the interventions is extensively trained in administering the standardised treatment protocols and rigorous procedures used for both the experimental and control groups. Routinely, during the course of the study, the physical therapist will meet with the study team to ensure consistency in the protocol and to discuss any concerns that may arise.

### Randomisation/blinding

#### Sequence generation and allocation concealment

Patients who agree to participate by signing an informed consent form will be stratified (to ensure sample homogeneity) into two groups based on the 1-h pad test results. The stratification will be performed according to the severity of SUI (mild leakage ≥ 2 to 10 g; moderate leakage 11 to 50 g) [17]. Next, the patients will be randomly allocated to one of three treatment groups (the Knack, PFMT and the Knack + PFMT). The allocation sequence will be generated by a research assistant ([name]) using a computer-generated random number table (http://randomization.com) [29] with a group ratio of 1:1:1 and will be concealed in sequentially numbered, sealed and opaque envelopes. The envelopes will be kept in a closed locker at the centre to which only the research assistant will have access. The envelopes will be given to the physical therapist ([name]) immediately prior to the first outpatient session.

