#### Primary outcome measure

The primary outcome measure will be the objective cure of UI as assessed by means of the 1-h pad test 6 months after randomisation. For the 1-h pad test, the women will be asked to wear pre-weighed pads and drink 500 ml of sodium-free liquid in < 15 min. After rest, they will be instructed to exercise for 30 min, including walking, climbing up and down five flights of stairs (10×), jumping (10×), coughing vigorously (10×), bending to pick up an object from the floor (10×) and washing hands for 1 min in running water. Before and after the test, the weight of the pad will be measured with a high-precision balance to determine the amount of leakage. For the 1-h pad test, an increase of 1 to 10 g represents mild incontinence and 11 to 50 g represents moderate incontinence. Women with urine leakage ≥ 2 g will be included because the study will be conducted in a tropical country [17]. The objective cure of urine loss after the intervention will be defined as leakage < 2 g. The pad test is considered a relevant tool for the assessment of UI treatment success and has been widely used in this type of study [30–32].

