Thus, according to the result of the pilot sample, at the 5% significance level, there is no significant difference between the groups in relation to the objective cure rate in the treatment of mild and moderate SUI, assessed by the 1-h pad test. Considering the premises: θ_1_= 42.9% and θ_2_= 71,4% (obtained through the analysis of the pilot sample), *δ* = − 7,14% (10% variation in relation to the response rate of the PFMT group, obtained through literature data [38], *r* = 1 (groups of equal sample sizes), *α* = 5% and *β* = 20% ⇒ power (1 – *β*) = 80%, we obtained a total of 122 patients (61 patients per group). Thus, considering a significance level of 5%, a sample of 122 patients (61 patients per group) has 80% power to show the non-inferiority of the knack technique compared to PFMT in the treatment of mild and moderate SUI, with a non-inferiority margin of − 7.14%, which corresponds to a variation of 10% in relation to the response rate of the PFMT group (gold standard), supposedly equal to 71.4% and assuming that the rate of response of the test group is 42.9%. The sample size calculation was based on the primary objective of comparing the Knack technique (experimental group) with PFMT (control group). However, we have a third group that associates the techniques PFMT + the knack, so, 183 participants will be recruited. It is also necessary to consider possible losses in the sample during the 6-month follow-up period, thus, we assume losses of 0 to 15% based on previously published studies [39, 40]. Thus, we will recruit nine more participants per group, increasing the total number of participants to 210.

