**Fig. 1 Fig1:**
[figure not shown]
CONSORT flowchart

Descriptive statistics will be performed for sample characterisation. Categorical variables will be expressed as the distribution of frequencies, and numerical variables by means of measures of central tendency and variability. The mean, standard deviation, 95% confidence interval, median and maximum and minimum values will be calculated for the analysis of the primary outcome measure (pad test). The primary outcome measure (pad test) will be compared within and amongst groups (the Knack, PFMT and the Knack + PFMT) (before and after intervention) using an ANOVA. All statistical analyses will be performed using the current version of SPSS software after the last patient undergoes the final assessment after intervention. The same approaches and statistical procedures used for the primary outcome measures will be employed for the analysis of the secondary outcome measures.

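### Randomisation is stratified by leakage severity, but the stated before/after ANOVA names no stratum term and does not use baseline as a covariate, so it gives up precision for nothing

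*Protocol article*

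**What the plan says.** Under Sequence generation and allocation concealment, consenting women are divided "into two groups based on the 1-h pad test results". "The stratification will be performed according to the severity of SUI": mild is 2 to 10 g and moderate is 11 to 50 g. They are then allocated "with a group ratio of 1:1:1" from a computer-generated random number table. Blocks are not mentioned.

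Under Primary outcome measure, the endpoint is "objective cure of UI as assessed by means of the 1-h pad test 6 months after randomisation", and "The objective cure of urine loss after the intervention will be defined as leakage < 2 g". The test that sets the stratum is therefore also the test that decides cure.

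Under Statistical analysis, "The primary outcome measure (pad test) will be compared within and amongst groups", "before and after intervention) using an ANOVA". The same procedures are to be used for the secondary outcomes. The abstract repeats the ANOVA. Neither place names the stratification factor or a baseline covariate.

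The sample size is for non-inferiority of the Knack to PFMT on cure: rates of 42.9% and 71.4% ("obtained through the analysis of the pilot sample"), a margin of −7.14 points, a 5% level, 80% power, 61 per group, raised to 70 per group for losses.

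**The concern.** Severity is the only stratification factor. A woman who starts at 40 g has further to go to get below 2 g than one who starts at 3 g, so severity is plausibly prognostic for cure. When a prognostic factor is used in allocation and then left out of the model, its variation stays in the residual error and the interval is wider than it needs to be.

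For the continuous outcomes, a group-by-time ANOVA on one before and one after measurement is the same as comparing mean change. Change scores subtract the whole baseline value. ANCOVA subtracts only the part that predicts follow-up, and it is at least as precise in a randomised comparison.

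What is at stake is efficiency, not bias. It matters because the trial has little power to spare on its main comparison.

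**Working it through.** **1. The plan's own figure.** With one-sided 5% (z = 1.645), 80% power (z = 0.842) and the unpooled variance:

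n = (1.645 + 0.842)² × [0.429 × 0.571 + 0.714 × 0.286] / (0.429 − 0.714 + 0.0714)² = 6.183 × 0.4492 / 0.04562 = 60.87, so 61 per group.

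The 61 reproduces, but the assumed difference of −28.5 points lies beyond the −7.14 margin, and the squared denominator hides the sign. Power to show non-inferiority at those rates is Φ(−0.2136/0.0858 − 1.645), about 0.002%. If both rates are 71.4%, power is 22% with 61 per arm and 24% with 70; 80% would need 496 per arm. This is a separate error. It sets the background for what follows.

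**2. Cure: variance saved by stratifying.** The article gives no cure rate by stratum and no stratum split. Assume equal strata with cure rates a gap g apart around a mean p. The overall variance p(1 − p) then equals the mean within-stratum variance plus g²/4. With p = 0.714, p(1 − p) = 0.2042:

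| Gap g | g²/4 | Within-stratum variance | Ratio to 0.2042 |
|---|---|---|---|
| 10 points | 0.0025 | 0.2017 | 0.99 |
| 20 points | 0.0100 | 0.1942 | 0.95 |
| 30 points | 0.0225 | 0.1817 | 0.89 |
| 40 points | 0.0400 | 0.1642 | 0.80 |

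At 61 per arm the half-width of the 90% interval falls from 13.5 points to between 13.4 and 12.1.

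**3. Cure: power at 70 per arm, no true difference.** Take mean cure of 65%, so that a 40-point gap means 85% and 45%. The unadjusted analysis uses SE = √(2 × 0.2275/70) = 8.06 points. With blocking within strata, the true SE is √(2 × within-stratum variance/70). Unadjusted power is Φ[(7.14 − 1.645 × 8.06)/true SE]; stratified power is Φ[7.14/true SE − 1.645].

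| Gap | True SE (points) | Unadjusted → stratified, formula | Simulated |
|---|---|---|---|
| 10 | 8.02 | 22.3 → 22.5% | 21.9 → 22.7% |
| 20 | 7.88 | 21.9 → 23.0% | 21.5 → 23.5% |
| 30 | 7.65 | 21.2 → 23.8% | 20.8 → 24.8% |
| 40 | 7.32 | 20.1 → 25.2% | 19.6 → 25.8% |

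The simulated gain runs from 0.8 to 6.2 points. The formula gives somewhat less, 0.3 to 5.0. Part of the difference is that the simulated stratified test had 5.3% error at the margin instead of 5%.

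**4. Dependence on blocking.** At the 40-point gap with fixed balance in each stratum, the unadjusted error at the margin is Φ(−1.645 × 8.06/7.32) = Φ(−1.81), about 3.5%. With simple allocation within strata, simulation gives 5.2%, so the test is not conservative. The simulated power gain is then 22.6 → 25.7%, about 3 points instead of 6.

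**5. Continuous outcomes.** Assume equal variances at baseline and follow-up with correlation ρ, which the article does not give. The relative variance is 2(1 − ρ) for change and 1 − ρ² for ANCOVA, so the ratio of interval widths is √[2/(1 + ρ)].

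- ρ = 0.3: √(1.40/0.91) = 1.24
- ρ = 0.5: √(1.00/0.75) = 1.15
- ρ = 0.7: √(0.60/0.51) = 1.08 to 1.09 (1.085)

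**The case against.** The strongest objection is that this rests on silence. Model terms are commonly left to an analysis plan, none is shown, and the article does not exclude a stratum term. Its stated reason for stratifying is a homogeneous sample, which is a design purpose and contradicts nothing. That stands as far as the missing stratum term alone goes. It does not cover the rest: the article does fix a method, a before/after ANOVA, and extends it to all outcomes. A better method that uses data already collected can fairly be recommended against a method that is stated.

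Three stronger readings are tempting, and the article does not support them.

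- A reader might infer that the ANOVA ignores baseline pad weight. It does not; baseline is the before measurement. The fair criticism is that this use of baseline is less efficient than a covariate.
- A reader might infer that the unadjusted test is conservative, with error near 3.4 or 3.5% instead of 5%. That needs blocking or a similar restriction within strata, which the article does not state, and it takes the top of the assumed range of gaps.
- A reader might infer that the missing adjustment explains the low power. It does not. The cause lies in the sample size premises, and a gain of 1 to 6 points on a base of 20 to 22% does not change the picture.

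It is also true that the cure figures compare two analyses of a cure-rate difference, neither of which is stated. An ANOVA on grams yields no interval for that difference. That mismatch is a larger issue in its own right. Whoever corrects it will have to choose between an adjusted and an unadjusted analysis, and that is where this point applies.

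**Conclusion.** The point holds as a modest matter of efficiency. The stated analysis names no term for the only stratification factor and treats baseline as a repeated measurement.

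The size cannot be derived from the article. For cure, the variance saving of about 1 to 20% and the power gain of about 1 to 6 points assume equal strata, cure rates 10 to 40 points apart, 70 per arm and blocking within strata; the gain is smaller without blocking. For continuous outcomes, the 9 to 24% excess width assumes a correlation of 0.7 to 0.3 and equal variances. If severity turns out to be weakly prognostic, the gain for cure is close to nil, but little is lost by adjusting.

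It ranks below the sample size error and the mismatch between the ANOVA and a binary non-inferiority endpoint.

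**What to change.** In the Statistical analysis section, and in the abstract where it repeats the method:

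- **Primary outcome.** Analyse the 6-month cure difference, Knack minus PFMT, as a stratum-adjusted risk difference with its confidence interval set against the −7.14 point margin. Use either a Mantel-Haenszel risk difference, or logistic regression with stratum and baseline pad weight followed by a marginal risk difference. Name one of them.
- **Continuous outcomes with a baseline value in Table 1.** Replace the before/after ANOVA with ANCOVA on the follow-up value, with the baseline value and the stratum as covariates.
- **Allocation.** State whether the sequence was blocked within strata, so that readers can judge how an unadjusted analysis would behave.

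The cost is wording only. Stratum and baseline pad weight are already recorded, and no visit, measurement or patient is added. The article reports 185 of 210 recruited, so the choice should be fixed before the outcome data are analysed; otherwise adjusting would look like a choice made after the results were seen.

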#### Blinding

The participants will not be blinded as to the received treatment. The researchers involved in data acquisition [outcome measures ([name])], data analysis and/or statistical analysis (professionals without knowledge of the results) will be blinded to the group allocation. The physical therapist responsible for the treatment ([name]) will not be blinded to the allocation of the patients in the groups because of the difficulties set by differences between techniques and, therefore, will not be involved in data acquisition, data analysis and/or statistical analysis. The epidemiological, clinical, allocation, randomisation and outcome data from the study will be stored in a virtual database. At the end of the study, the results will be made available to researchers who did not have contact with the participants as well as to statisticians blinded to the groups, and the researchers and statisticians will perform the data analysis.

